### Data management

Data will be collected by using data sheets. All data obtained will be safely kept electronically over a period of 6 years if not published, and 2 years if published. Data will be backed up onto Google Drive and a password-protected external hard drive.

The informed consent and questionnaire hard copies will also be stored securely in a locked drawer in the researcher’s code-protected office for a period of 6 years. After a period of 6 years, the hard copies with participants’ information will be deleted and destroyed by the researcher. In the case of minors, health records will be kept until the minor’s 21st birthday as required by national legislation.

### Statistical analysis

All identifiers will be removed. Descriptive statistics will be used to analyse the gathered data during the time of the study. Frequencies and percentages for categorical data and means and standard deviations or medians and percentiles for numerical data will be calculated. The data will be tabulated; trends will be presented in the form of graphs. A statistician assisted with the planning of data analysis. The statistical analysis for each objective will now be presented:

1.To determine the effects of telerehabilitation services for patients who have orthopaedics conditions (arthroplasty).

Categorical variables (symptoms, pain, function and daily living, function, sports and recreational activities, quality of life) will be summarised by using frequencies and percentages. Bivariate analysis between groups for total hip replacements and total knee replacements will be performed by using Chi squared test if 25% of the expected frequencies are above five or by using Fisher’s exact test if the assumption is not valid. Similarly, bivariate associations between gender, age and compliance with the outcomes (symptoms, pain, function and daily living, function, sports and recreational activities, quality of life) will be assessed by using Chi squared test or Fisher’s exact test:

2.To determine the effects of telerehabilitation services for patients who have NMS conditions (chronic low back pain).

Categorical variables (symptoms, pain, function and daily living, function, sports and recreational activities, quality of life) will be summarised by using frequencies and percentages. Whilst age is a continuous/numerical variable and the outcomes being categorical variables, with three groups, an analysis of variance (ANOVA) test is used if data are normally distributed or Kruskal Wallis test is used if they are not normally distributed:

3.To determine the effects of telerehabilitation services for patients who have paediatric conditions.

Categorical variables will be summarised by using frequencies and percentages:

4.To determine the patient or caregiver and physiotherapist experiences in the rollout of telerehabilitation services.

Frequencies and proportions will be used to summarise categorical variables. The two samples proportions test will be used to compare if there are any differences between the Yes or No responses. Comparisons between proportions with categorical variables will be performed by using the Chi squared test with the condition that the assumption is met:

5.Qualitative information will be gathered from two sources. The therapist’s experiences will be collected as positive, negative, challenges and other, and if further subthemes emerge from those categories, it will be described verbatim. In the subjective framework of questions, patients are asked a directed open-ended question on their experience of the call and the telerehabilitation sessions. The responses will also be categorised into themes that emerge.

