#### Outcome measures

The Hip Disability and Osteoarthritis Outcome Score Joint Replacement (HOOS JR), which is a self-reported questionnaire on performance pain and functional status, with good reliability and construct validity, will be used for patients with hip arthroplasty (Lyman et al. 2016). The Knee Injury and Osteoarthritis Outcome Score (KOOS JR) will be used for knee arthroplasty patients. The KOOS JR is a knee-specific outcome measure assessing pain, symptoms and function related to their knee and associated problems (Lyman et al. 2016). The KOOS has been validated in multiple populations, activity levels and ages. Divergent and convergent construct validities have been determined when comparing to the SF-36 a health survey. The HOOS JR and KOOS JR will be used as an objective outcome measure for participants with arthroplasty.

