### Outpatient chronic low back pain physiotherapy specialist area

#### Procedures

The sample will consist of participants who had been assessed as being suitable for group exercise classes, after having completed individual face-to-face physiotherapy sessions. A similar procedure as for arthroplasty telerehabilitation session will be followed for the above cohort of patients. The telerehabilitation session will follow an adapted framework of questions, which will explore the patient’s functional ability, pain score and self-management principles (Appendix 2). At every session, the Keele STarT Back screening tool will be used as the outcome measure to monitor patient progress and to categorise patients as low, medium and high risk.

Following the first session of telerehabilitation, those patients who fall into the high-risk category will be called back for a face-to-face consultation session and managed accordingly. Patients who fall into the medium- and low-risk category will be managed via telerehabilitation, wherein a specific category or level of a HEP will be prescribed and sent to the patients via their preferred method of communication. Follow-up appointments will be at 2–4-week intervals. Based on the patients’ report and presentation, exercises and advice will be progressed. Once patients have reached a score of less than three on their Keele STarT Back screening assessment tool, they can be discharged from physiotherapy.

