#### Outcome measure

The Keele STarT Back screening tool is available in English and Zulu, and according to Bruyère et al. (2014) the test-retest reliability of the Keele STarT back screening tool total score was excellent with an intraclass correlation coefficient of 0.90. The validity was found to be moderate to high in Pearson’s correlation for questions three to nine and a low correlation for questions one and two (Bier et al. 2017). This tool is designed to screen primary care patients with low back pain and serves as a prognostic indicator for initial decision-making. This tool allows clinicians to group low back pain patients into three categories of risk.

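### The outcome list in the statistical analysis does not match the questionnaires the protocol names for arthroplasty and chronic low back pain

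*Protocol article*

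**What the plan says.** All references are to the protocol article.

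- **Statistical analysis, objective 1 (arthroplasty).** The outcomes are given as: "Categorical variables (symptoms, pain, function and daily living, function, sports and recreational activities, quality of life) will be summarised by using frequencies and percentages". Hips and knees are then to be compared: "Bivariate analysis between groups for total hip replacements and total knee replacements will be performed by using Chi squared test", with Fisher's exact test as the fallback. Gender, age and compliance are to be related to the same outcomes by the same two tests.
- **Statistical analysis, objective 2 (chronic low back pain).** The outcome sentence is repeated word for word. The text then continues: "Whilst age is a continuous/numerical variable and the outcomes being categorical variables, with three groups", and applies ANOVA or Kruskal-Wallis.
- **Outcome measures, arthroplasty section.** "The HOOS JR and KOOS JR will be used as an objective outcome measure for participants with arthroplasty". The hip form is introduced as one "which is a self-reported questionnaire on performance pain and functional status". For the knee form: "The KOOS JR is a knee-specific outcome measure assessing pain, symptoms and function related to their knee and associated problems".
- **Procedures, chronic low back pain section.** At every session, "the Keele STarT Back screening tool will be used as the outcome measure to monitor patient progress". The session questions also cover functional ability, a pain score and self-management.
- **Outcome measure, chronic low back pain section.** The text refers to the tool's total score and adds: "This tool allows clinicians to group low back pain patients into three categories of risk".

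**The concern.** The analysis section states its outcome variables, and they differ from what the outcome sections say will be measured. This is a conflict between two stated passages, not detail that an article would leave to a fuller plan.

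An analyst following the text would look for sports/recreation and quality-of-life variables that no described instrument yields. The same analyst would find no instruction naming the HOOS JR, KOOS JR or STarT Back scores as the quantities to analyse. What counts as the effect of telerehabilitation would then be settled after the data are in, which leaves room for selective reporting. Two of the three effect objectives in the statistical section are touched: arthroplasty and low back pain, but not paediatrics.

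A smaller inconsistency sits beside this. Age is tested as a categorical variable in objective 1, with no age bands given, and is called numerical in objective 2.

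**Working it through.** The article states no sample size, power or significance level that bears on this, so there is no figure to reproduce. The check is a match of the listed domains against the instruments as the article describes them.

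**Step 1: read the list.** The wording runs together, with function appearing twice. I read it as five domains: symptoms; pain; function in daily living; function in sports and recreation; quality of life. This reading is an assumption.

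**Step 2: match each domain to a described source.**

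| Listed domain | HOOS JR (hip) | KOOS JR (knee) | STarT Back (low back pain) | Low back pain session questions |
|---|---|---|---|---|
| Symptoms | no | yes | no | no |
| Pain | yes | yes | no | yes (pain score) |
| Function, daily living | yes | yes | no | yes (functional ability) |
| Function, sports/recreation | no | no | no | no |
| Quality of life | no | no | no | no |
| **Described source** | **2 of 5** | **3 of 5** | **0 of 5** | **at most 2 of 5** |

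Here yes means that the article describes the source as covering the domain, and no means that it does not. STarT Back scores 0 because it is described as giving a total score and a risk category, not any of the listed domains.

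**Step 3: hip versus knee.** The comparison needs a domain described for both forms. The hip set is {pain, function} and the knee set is {pain, symptoms, function}. Their intersection is {pain, function}, so 2 of 5. Symptoms can be tabulated for knees only, and the last two domains for neither group.

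**Step 4: other possible sources.** Table 1, which forms the arthroplasty session notes, asks about pain, mobility and walking distance, exercises, activities of daily living and current difficulties. It has no sports or quality-of-life question. The low back pain session framework is described as functional ability, pain score and self-management, again without either.

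**Step 5: the declared outcome in objective 2.** Neither the STarT Back total score nor its risk category appears in the objective 2 variable list. The only possible trace is the mention of three groups in the age comparison. The tool does produce three risk categories, so the reading is plausible, but the text does not label the groups.

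**Step 6: age.** Objective 1 uses chi-squared or Fisher's exact for age against outcome. Objective 2 calls age continuous/numerical and uses ANOVA or Kruskal-Wallis. The same variable is treated in two ways without a reason given.

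**The case against.** Several points on the other side carry weight.

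- **The mismatch is partial.** A reader might infer that the two objectives cannot be analysed at all. The documents do not support that. Pain and function have a described source for hips and knees, symptoms have one for knees, and the back pain sessions collect pain and functional ability. This stands and limits the point to part of the list.
- **The three groups may be the STarT Back risk categories.** If so, the declared outcome does enter objective 2, though unlabelled. This is plausible. It would serve only the age comparison, and the summary of effects would still be written for a different list.
- **Numerical summaries are promised in general.** The opening of the statistical section provides means or medians for numerical data, which could cover the questionnaire scores. That is so, but the paragraphs for objectives 1 and 2 call the outcomes categorical and do not name the scores.
- **The instrument name may be the error, not the list.** The arthroplasty outcome text moves from the KOOS JR to the KOOS when it cites validation. The longer list may therefore be the intended one. This stands, and the fix must not presume which side is wrong.
- **Appendices 1 and 2 are not shown.** It would be too strong to say that the missing variables will not exist. The supportable statement is that no source is described for them.
- **Age in objective 2 is already numerical.** Only objective 1 needs a change.

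A reader might also want to put a figure on the information lost by categorising scores. The plan gives no cut-points, so no such figure can be supported. Finally, the analysis is largely descriptive and a pilot is meant to catch errors in method. That lessens the damage but does not remove the contradiction.

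**Conclusion.** The point holds as an internal contradiction of limited extent. For arthroplasty, two of the five listed domains have no described source, a third (symptoms) has one for the knee form only, and the planned hip-versus-knee comparison is supported in both groups for two of five. For chronic low back pain, the list is carried over from arthroplasty, and the declared outcome measure is not named in the analysis, except possibly as the unlabelled three groups. Age is handled inconsistently between objectives 1 and 2, and the fault lies in objective 1.

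This rests on the five-domain reading of the list and on the article's own descriptions of its instruments. If the unshown appendices or a fuller plan name a source for the extra domains, the contradiction becomes one of cross-reference. The article would still need to name that source.

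**What to change.** Reconcile the outcome-measure sections with the statistical section before analysis.

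1. **Objective 1, if the JR forms are the instruments used.** Make the HOOS JR score (hips) and the KOOS JR score (knees) the outcomes, each summarised numerically within its own group. Limit any hip-versus-knee comparison to content that both forms measure.
2. **Objective 1, if the longer domain list is intended.** Name the instrument that supplies it and correct the outcome-measure section accordingly.
3. **Objective 2.** Replace the carried-over list with the STarT Back total score and risk category, plus the session pain score. State what the three groups are.
4. **Age.** Treat it as numerical in objective 1, as objective 2 already does.

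If the named instruments are right, the cost is rewording two analysis paragraphs, with no new data. If the longer list was intended and no instrument collecting it is in use, another questionnaire and further data collection would be needed, so the question should be settled early.

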### Objectives

The objectives of the study are as follows:

To determine the patient and/or caregiver and physiotherapist experiences in the rollout of telerehabilitation for selected outpatient groups.To determine the effects of telerehabilitation services for patients who have orthopaedic conditions (arthroplasty), NMS conditions (chronic low back pain) and paediatric conditions (cerebral palsy, developmental delay and orthopaedic conditions).

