## Methods and design

Purposive sampling will be used for this prospective mixed method study. Patients who have previously attended the outpatient physiotherapy department for the management of their orthopaedic, NMS and paediatric conditions prior to the national lockdown and those who had to have their appointments cancelled will be invited to participate. These patients will be selected as they are long-term patients requiring ongoing physiotherapy to prevent further disability but are not prioritised for face-to-face consultations because of the COVID-19 pandemic. Initially, a pilot study will be conducted to determine the sample size and rule out any errors in the methodology, and thereafter the study will be expanded.

A standard operating procedure (SOP) will be developed for arthroplasty (orthopaedic) and patients with chronic low back pain (NMS), cerebral palsy, developmental delay and acute orthopaedic conditions (paediatrics) with the purpose of providing an outline for therapists to deliver telerehabilitation services effectively and ethically. For each area, a database will be created containing videos and images of relevant interventions related to the specific condition being treated. Exercise prescription will commence from the patients’ current level of function and will be progressed as per the criteria described in the section’s guidelines of management of arthroplasty, chronic low back pain and paediatric patients. A section on general advice and health education will also be included.

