Findings will be disseminated by means of publications in relevant accredited journals like the South African Health System Review to advise policymakers on the efficacy of such systems. It will be presented at various conferences and symposiums and, in addition, will be presented in several forums like Physiotherapy Forum, Rehabilitation Forum, CHBAH Research Day, Ekurhuleni Research Day and other symposiums to disseminate the information in the context it was studied on.

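### The tests planned for the effects objectives do not address the effect of telerehabilitation, and no estimate of within-patient change is specified for any cohort

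*Protocol article*

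**What the plan says.** The Objectives section gives the clinical aim as "To determine the effects of telerehabilitation services for patients who have orthopaedic conditions (arthroplasty), NMS conditions (chronic low back pain) and paediatric conditions". The design is described thus: "Purposive sampling will be used for this prospective mixed method study". No comparator group is described. Sample size is deferred: "a pilot study will be conducted to determine the sample size and rule out any errors in the methodology".

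The Statistical analysis section announces an analysis for each objective and assigns the following:

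- **Arthroplasty:** frequencies and percentages. Then "Bivariate analysis between groups for total hip replacements and total knee replacements will be performed" by chi-squared or Fisher's exact test, and "bivariate associations between gender, age and compliance with the outcomes" by the same tests.
- **Chronic low back pain:** frequencies and percentages, and age compared across three outcome groups by ANOVA or Kruskal-Wallis.
- **Paediatrics:** frequencies and percentages.

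The Outcome measures section for arthroplasty says that the HOOS JR "will be used for patients with hip arthroplasty" and assigns the KOOS JR to knees. In the back pain section, the Keele STarT Back tool is completed at every session. Appendix 4 sets a modified GAS goal for each child and reviews it at 3 months.

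On use of the results, the Problem statement speaks of exploring effectiveness. The Discussion speaks of exploring effectiveness and understanding efficacy, and plans publication "to advise policymakers on the efficacy of such systems".

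**The concern.** An effects objective needs at least an estimate of how patients changed while they received the service. The tests assigned to it ask other questions: whether hips differ from knees, whether outcome category goes with gender, age or compliance, and whether age differs between back pain outcome groups. A reader who followed the plan exactly would obtain p-values for all of these and still have no estimate of change.

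Two features make it worse. Hips and knees are scored on different forms, so a hip-knee difference cannot be told apart from a difference between forms. And with no comparator, even a well-estimated change could reflect natural recovery or regression to the mean, whereas the Discussion points towards advice to policymakers on efficacy.

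**Working it through.** **Step 1: each objective beside its planned analysis.**

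| Cohort | Instrument described | Planned analysis | Estimates within-patient change? |
|---|---|---|---|
| Hip arthroplasty | HOOS JR | Frequencies; hip versus knee; gender, age, compliance | No |
| Knee arthroplasty | KOOS JR | As for hips | No |
| Chronic low back pain | STarT Back, every session | Frequencies; age across three outcome groups | No |
| Paediatrics | GAS goal reviewed at 3 months (Appendix 4) | Frequencies; GAS not named | No |

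The remaining planned tests (two-sample proportions, chi-squared) belong to the experience objective.

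**Step 2: outcome domains beside the instruments.** The analysis section lists symptoms, pain, function and daily living, function, sports and recreation, and quality of life, for arthroplasty and again for back pain. The Outcome measures section describes the HOOS JR as covering pain and functional status, and the KOOS JR as covering pain, symptoms and function. Neither is said to measure sports and recreation or quality of life. For back pain the only outcome measure named is the STarT Back tool, described as sorting patients into three risk categories. The listed variables therefore do not match the forms described.

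**Step 3: what the hip-knee test can and cannot see.** The article states no alpha, sample size or expected proportions, so there is no figure to reproduce. These inputs are all assumed, for illustration: two-sided alpha 0.05; 30, 50 or 100 patients per joint; a good or not-good outcome; 30% good at baseline in both joints; nobody worsens.

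*(a) Equal improvement in both joints.* In 2,000 simulated trials per setting, the hip-knee chi-squared test rejected as follows:

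| Patients per joint | 30% to 50% good | 30% to 70% good |
|---|---|---|
| 30 | 4.7% | 4.3% |
| 50 | 6.7% | 5.2% |
| 100 | 6.4% | 4.3% |

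That is roughly its alpha, however large the shared improvement.

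*(b) No change in anyone, but hips at 70% good and knees at 40% throughout.* Power = Φ{[0.30 − 1.96·√(2·0.55·0.45/n)] / √[(0.70·0.30 + 0.40·0.60)/n]}. For n = 30 this is Φ[(0.300 − 0.252)/0.1225] = Φ(0.394) = 0.65. For n = 50 it is 0.87, and for n = 100 it is 0.99.

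*(c) A paired test on the data in (a), each joint analysed separately.* With no patient worsening, the exact McNemar test rejects at 6 or more improvers, since 2·0.5⁶ = 0.031 while 2·0.5⁵ = 0.063. Going from 30% to 50% good, each patient improves with probability 0.20. P[Bin(n, 0.20) ≥ 6] is 0.57 for n = 30, 0.95 for n = 50 and above 0.99 for n = 100. Going from 30% to 70%, the probability is 0.40 and the result is above 0.99 even at n = 30. Pooling both joints (60 patients) would raise the 0.57 to 0.99, but pooling mixes the two forms and is not what is recommended.

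The hip-knee test is thus insensitive to shared improvement and can reject when nobody changes.

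**The case against.** The strongest reply is that the plan is not silent on progress. It promises graphs of trends, collects the STarT Back tool at every session, and reviews each child's goal at 3 months. A reader might infer that no change of any kind could be shown. The documents do not support that: trend graphs could display a course over time, and the paediatric frequencies could tabulate goals met. But the graphs are tied to no variable, time point or estimate, and the analysis section does not name GAS. The supportable statement is that no estimate of change is specified.

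Secondly, a reader might infer that efficacy is the study's declared conclusion. It is not. The abstract's Conclusion concerns whether the service is feasible, and Significance of the study says the same. Efficacy appears only in the Discussion, and effectiveness is something to be explored. This part is a wording correction.

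Thirdly, this is a condensed article, and Appendices 1 and 2 are not shown. The absence of measurement times for the HOOS JR and KOOS JR is therefore no finding. Nor is multiplicity: with no alpha or sample size stated, a false-positive count would rest on invented inputs.

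The core stands. The article does not leave the effects analysis to another document. It assigns specific tests to it, and they answer different questions.

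**Conclusion.** The point holds in limited form. For objectives 1 and 2 the inferential tests do not address the effect of telerehabilitation. For all cohorts, no estimate of within-patient change is specified. Some listed outcome domains do not match the instruments described. This rests on reading the analysis section against the objectives and instruments, and needs no numerical assumption. The rejection rates and powers above are illustrations under assumed inputs and are not estimates for this study.

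A paired analysis would answer the descriptive question of how much patients changed. It would not turn the study into evidence of efficacy, because no comparator is described. This should be put right before analysis, since the effects objectives otherwise go unanswered.

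**What to change.** 1. **Arthroplasty and back pain.** Make the primary analysis the within-patient change from the first telerehabilitation session to a pre-set follow-up session, with a 95% CI, separately for HOOS JR, KOOS JR and STarT Back.
2. **Patients who leave early.** Include those discharged or moved to face-to-face care, using their last available score, and report their numbers. This matters because discharge depends on outcome (a functional goal reached, or a STarT Back score below three) and high-risk back pain patients are called back for face-to-face care after the first session. A last score at discharge is favourable by selection, and a patient with only a first-session score contributes zero change, so show both groups separately as well.
3. **Paediatrics.** Report the proportion achieving or partly achieving the 3-month GAS goal, with a 95% CI, and name GAS in the analysis section.
4. **Hip versus knee.** Drop this test as evidence of effect, or label it descriptive.
5. **Outcome list.** Reconcile the listed domains with what each instrument measures, cohort by cohort.
6. **Wording.** In the Problem statement and Discussion, replace effectiveness and efficacy with change during telerehabilitation, alongside feasibility and experience.

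The cost is a more modest claim and a fixed measurement point for forms already in use. Because sessions are only approximately spaced and discharge is goal-driven, some discharged patients may have to be contacted again if a score at the fixed point is wanted.

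### The stated condition for chi-squared (25% of expected counts above five) is wrong as written: it disables the Fisher fallback in any 2x2 table of more than 20 patients, though the resulting error is confined to unbalanced tables with rare categories

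*Protocol article*

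**What the plan says.** Under objective 1 (arthroplasty) in the Statistical analysis section, the article sets a numerical rule for choosing the test. The comparison is described as "Bivariate analysis between groups for total hip replacements and total knee replacements". The rule is that it is "performed by using Chi squared test if 25% of the expected frequencies are above five". When that condition fails, Fisher's test takes its place. The next sentence extends the same pair of tests to gender, age and compliance against each listed outcome, which "will be assessed by using Chi squared test or Fisher’s exact test".

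Under objective 4 (experiences), comparisons of proportions are "performed by using the Chi squared test with the condition that the assumption is met". No threshold and no alternative test are given there.

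The article states no sample size. Under Methods and design it says: "Initially, a pilot study will be conducted to determine the sample size". It gives no significance level, no hip and knee numbers and no category frequencies, and it does not say whether chi-squared carries a continuity correction. Nothing elsewhere corrects the 25% or adds a minimum expected count.

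**The concern.** The customary condition limits the share of cells with small expected counts to about 20-25%. The article applies a figure of that size to the share of cells with adequate counts, which is close to the reverse. The rule exists to send sparse tables to an exact test, and as written it sends nearly all of them to the large-sample approximation.

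Sparse tables are plausible here. This is purposive sampling at one hospital, arthroplasty is one of several condition groups, and it is split again into hips and knees and then by gender, age and compliance. In a sparse, unbalanced table the uncorrected chi-squared p-value can be well below the exact one, so a single patient can produce a nominally significant association. Because this is a stated decision rule, it is not a detail that a condensed article has left to a fuller plan.

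**Working it through.** The 25% is a decision threshold, so there is no plan figure to reproduce. The check is what the rule permits and what follows from it. I read it as at least 25% of expected counts above five.

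**1. Cells allowed at or below five.** Formula: cells − ceil(0.25 × cells).

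| Table | Must exceed five | May be five or less |
|---|---|---|
| 2x2 | 1 of 4 | 3 (75%) |
| 2x3 | 2 of 6 | 4 (67%) |
| 2x4 | 2 of 8 | 6 (75%) |
| 2x5 | 3 of 10 | 7 (70%) |

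So 75% is a ceiling, reached for some table sizes.

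**2. When Fisher's test is reached in a 2x2 table.** The four expected counts sum to N, so the largest is at least N/4. If N > 20, then N/4 > 5 and at least one cell in four exceeds five. The condition always holds and Fisher's test is never selected. This step needs no assumption about group sizes or frequencies. Example: margins 20/4 by 20/4 give expected counts 16.67, 3.33, 3.33 and 0.67. One of four exceeds five, so the rule selects chi-squared.

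**3. Single tables (constructed, uncorrected Pearson).**
- Hips 2/10, knees 1/40: expected counts 10×3/50 = 0.6, 40×3/50 = 2.4, 9.4 and 37.6. X² = 1.4² × (1/0.6 + 1/2.4 + 1/9.4 + 1/37.6) = 4.34, p = 0.037. Fisher p = 0.098.
- Hips 1/10, knees 0/40: chi-squared p = 0.043, Fisher p = 0.20.
- Hips 1/4, knees 0/40: expected counts 0.09, 3.91, 0.91 and 39.09. Chi-squared p = 0.0014, Fisher p = 0.091. This is an extreme table with one event.

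**4. Type I error by exact enumeration.** Assumed: two-sided nominal 5%, a common category probability p, and group sizes n1 and n2. Size = Σ over a, b of Bin(a; n1, p) × Bin(b; n2, p) × 1{test chosen by the rule rejects}. A table with an empty margin counts as no rejection. The last column uses chi-squared only if at least 80% of expected counts exceed five, and Fisher's test otherwise.

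| Groups | Category | Written rule, uncorrected | Written rule, continuity-corrected | 80% rule |
|---|---|---|---|---|
| 10/40 | 3% | 9.1% | 1.1% | 1.2% |
| 10/40 | 5% | 7.8% | 1.5% | 1.8% |
| 10/40 | 10% | 4.5% | 1.4% | 2.4% |
| 10/40 | 20% | 4.3% | 1.5% | 2.9% |
| 8/30 | 5% | 9.3% | 0.3% | 1.4% |
| 8/30 | 10% | 6.2% | 0.9% | 1.7% |
| 8/30 | 20% | 4.2% | 1.2% | 2.2% |

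With groups of 15/35 the written rule (uncorrected) gives 2.9-5.2% for categories of 3-50%. With 20/30 it gives 0.9-5.6%. With 25/25 it gives 0.6-5.5% for 3-30%; at 50% it gives 6.5%, but so does the 80% rule.

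**5. Larger tables.** A 2x4 table with rows 5/38 and columns 20, 20, 2, 1 has exactly two of eight expected counts above five and a smallest count of 5×1/43 = 0.12. With margins fixed, uncorrected chi-squared has size 12.7%. Five other sparse 2x3 and 2x4 tables that satisfy the rule gave 2.0-5.9%.

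**The case against.** The strongest objection concerns consequence. The inflation needs three things together: strong imbalance, a rare category and an uncorrected statistic. The article supplies none of these; the sizes and frequencies above are assumptions. Even at 10/40 the written rule is near nominal once the category reaches 10%, and with the usual 2x2 continuity correction the 9.1% becomes 1.1%. All of this stands.

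It also stands that the analysis is mainly descriptive and single-group, that these bivariate comparisons do not estimate the effect of telerehabilitation, and that no decision hangs on them. Nor is the repair free: at 25/25 with a 10% category the conventional rule has a true size of about 1%, against 4.9% under the written one.

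That the wording is probably a slip also has force, but it does not rescue the text. An analyst who follows it gets the wrong test in some tables, and one who corrects it silently departs from the published rule.

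Two stronger readings are tempting and unsupported. A reader might infer that p-values will be far too small in small, uneven subgroups generally; the enumeration shows otherwise. A reader might also count objective 4 as a second instance of the error. Its wording, "Chi squared test with the condition that the assumption is met", does not repeat the 25%; it leaves a condition without a threshold, which an article may leave to a fuller document.

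**Conclusion.** The condition under objective 1 is wrong as written. It tolerates up to 75% of cells at or below five, sets no floor, and in every 2x2 table with more than 20 patients makes the Fisher fallback inoperative. That much follows from the article's words and arithmetic alone.

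The size of the harm rests on assumptions. With 10/40 groups, a nominal 5% level and uncorrected Pearson, it amounts to 7.8-9.1% for categories of 3-5% and disappears by 10%. In the settings examined, harm is confined to unbalanced tables with rare categories, and for 2x2 tables it also depends on not using a continuity correction. For secondary comparisons in a largely descriptive study, that makes this a moderate to minor correction and not a threat to the study's conclusions.

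**What to change.** Replace the condition under objective 1 with: chi-squared if at least 80% of expected counts are five or more and none is below one; otherwise Fisher's exact test, using its r x c extension for larger tables. Say that the rule covers both the hip-versus-knee comparison and the gender, age and compliance associations, and let the assumption mentioned under objective 4 refer to the same rule.

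The change is one sentence and a cross-reference, to be made before the tables are seen. The cost is conservative p-values in sparse tables: a true size of about 1-3% in the unbalanced settings above, with some loss of power.
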